## **5.6 Allocation of participants**

The study participants will be allocated to the intervention or control group depending on which community they were enrolled at the time of the baseline screening.

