#### **5.0 METHODOLOGY**

##### **5.1 Study design**

This is a Quasi-experimental study with repeated measures, collaboration between Department between the research team from Department of Social and Preventive Medicine, University of Malaya and community volunteers from Malaysian Diabetes Associations (MDA), local residential committees and primary health clinics.

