## 5.2 Study area

The study will be conducted in two sub-urban communities in Seremban, Negeri Sembilan, Malaysia. Based on 2010 report [33-35], two communities i.e., Ampangan and Senawang with similar demographic and socioeconomic characteristics were selected.

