## **5.8 Sample size estimation**

Referring to the study by Kulzer et al [42] using a group based lifestyle intervention study to prevent diabetes mellitus; mean weight loss and duration of physical activity per week were significantly higher while fasting glucose was significantly lower in the intervention group compared to the control group after 12 months follow up. Using the sample size calculation from STATA

program, with power of 80% and significant level preset at 0.05, using different indicators, the calculated sample sizes are as the following:

|                                        | Duration of physical activity (minutes) | Fasting blood glucose (mg/l) | Weight loss (kg) |
|----------------------------------------|-----------------------------------------|------------------------------|------------------|
| Mean difference 1                      | 17.9                                    | 1.8                          | 3.8              |
| Mean difference 2                      | 46.6                                    | -4.3                         | 1.4              |
| Standard deviation 1                   | 63.8                                    | 13.1                         | 5.2              |
| Standard deviation 2                   | 95.5                                    | 11.3                         | 4.1              |
| Calculated Sample size group 1         | 122                                     | 64                           | 60               |
| Calculated Sample size group 2         | 122                                     | 64                           | 60               |
| Final sample size (with 30% attrition) | 122 x 2 = 244                           | 83 x 2 = 166                 | 78 x 2 =156      |

Based on the above, the largest sample size will be used in this proposed study to ensure adequate power for most outcome measures. Therefore, 244 subjects will be require for this study.

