## 12.0 DATA ANALYSIS

Patient demographic, clinical variables and baseline value will be compare between groups by the use of independent t-test for normally distributed variables and Mann Whitney test for non-normally distributed variables. Chi-square test will be use for discrete variables. The analysis will be done according to the intention-to-treat (ITT) principle. The missing values will be replaced by

the last readings carried forward. General Linear Model repeated measures ANOVA will be conducted to examine the changes overtime within-groups and between-groups. In the repeated measures model, the baseline value of co-morbidities, medication used, smoking and alcohol consumption were used as covariates in analysis for lipid profiles and blood pressure measurements. The outcome results from baseline to follow up at 6 months and 12 months will be presented as mean group differences, 95% confidence interval, p value and partial eta squared. A p-value of  $<0.05$  was considered statistical significant and effect size as proposed by Cohen (1998) were (0.01= small effect, 0.06= moderate effect and 0.14= large effect [65]. All statistical analysis will be performed using the SPSS software version 19.0 (SPSS Inc, 2009, Chicago, Illinois)

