## 16.0 GANTT CHART

| Activities :                                           | Year 2011 |     |     |     |     |     |     |     |     |     |     |     |
|--------------------------------------------------------|-----------|-----|-----|-----|-----|-----|-----|-----|-----|-----|-----|-----|
|                                                        | Jan       | Feb | Mar | Apr | May | Jun | Jul | Aug | Sep | Oct | Nov | Dec |
| 1. Preparation of study proposal                       |           |     |     |     |     |     |     |     |     |     |     |     |
| 2. Submission to ethical review board                  |           |     |     |     |     |     |     |     |     |     |     |     |
| 3. Protocol approval from UMMC ethical board           |           |     |     |     |     |     |     |     |     |     |     |     |
| 4. Submission to IPPP for post-graduate research grant |           |     |     |     |     |     |     |     |     |     |     |     |
| 5. Preparation of study materials                      |           |     |     |     |     |     |     |     |     |     |     |     |
| 6. Health screening and recruitments                   |           |     |     |     |     |     |     |     |     |     |     |     |
| 7. Training of the trainers                            |           |     |     |     |     |     |     |     |     |     |     |     |
| 8. Randomization & Baseline data collection            |           |     |     |     |     |     |     |     |     |     |     |     |
| 9. Lifestyle interventions                             |           |     |     |     |     |     |     |     |     |     |     |     |
| Activities :                                           | Year 2012 |     |     |     |     |     |     |     |     |     |     |     |
|                                                        | Jan       | Feb | Mar | Apr | May | Jun | Jul | Aug | Sep | Oct | Nov | Dec |
| 10. Lifestyle interventions                            |           |     |     |     |     |     |     |     |     |     |     |     |
| Activities :                                           | Year 2013 |     |     |     |     |     |     |     |     |     |     |     |
|                                                        | Jan       | Feb | Mar | Apr | May | Jun | Jul | Aug | Sep | Oct | Nov | Dec |
| 11. Data collection                                    |           |     |     |     |     |     |     |     |     |     |     |     |

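### Each arm is a single community, so the programme cannot be separated from other between-community differences in change, and the 5% error rate and stated power hold only if that variance is zero

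*Protocol*

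**What the plan says.** - **Design.** Section 5.1: "This is a Quasi-experimental study with repeated measures".
- **Communities.** Section 5.2: "two communities i.e., Ampangan and Senawang with similar demographic and socioeconomic characteristics were selected".
- **Allocation.** Section 5.6: participants are "allocated to the intervention or control group depending on which community they were enrolled at the time of the baseline screening".
- **Sample size.** Section 5.8 compares two group means using individual standard deviations, "with power of 80% and significant level preset at 0.05". It gives 122 (physical activity), 64 (fasting glucose) and 60 (weight) per group, and adopts the largest, 244 in total. No ICC, design effect or number of clusters appears.
- **Analysis.** Section 12.0: "General Linear Model repeated measures ANOVA will be conducted to examine the changes overtime within-groups and between-groups". Group differences are reported with 95% confidence intervals and p-values against 0.05. No allowance for community is described.
- **Limitations.** Section 13.0 covers measurement bias, information bias and dropout. It does not say that arm and community coincide.
- **Schedule.** Section 16.0 lists "Randomization & Baseline data collection" as an activity.

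**The concern.** Arm and community are the same variable. Anything that makes glucose, weight or activity change differently in the two places over the 6 or 12 months, such as a local event or campaign, enters the estimated programme effect, and nothing in the data can remove it.

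The individual-level analysis also takes its error term only from variation between people within a community. It therefore understates uncertainty about the programme whenever communities differ at all in how they change.

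The general objective (section 4.0) is to assess effectiveness. Without a caveat, p < 0.05 would be read as meeting that objective, when it would show only that two communities changed differently. This applies to every between-group result, including the three glycaemic primary outcomes.

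**Working it through.** **Inputs (section 5.8).** The rows "Mean difference 1" and "Mean difference 2" give:
- physical activity 17.9 and 46.6 (difference 28.7), SDs 63.8 and 95.5;
- fasting glucose 1.8 and −4.3 (difference 6.1), SDs 13.1 and 11.3;
- weight 3.8 and 1.4 (difference 2.4), SDs 5.2 and 4.1.

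The SDs are taken as SDs of change.

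**Reproducing the plan.** For independent individuals, two-sided 0.05 and 80% power, n per group = (1.96 + 0.8416)² × (SD1² + SD2²) / difference².
- Fasting glucose: 7.849 × 299.30 / 37.21 = 63.1, so 64 (stated 64).
- Weight: 7.849 × 43.85 / 5.76 = 59.75, so 60 (stated 60).
- Physical activity: 7.849 × 13190.69 / 823.69 = 125.7, so 126 (stated 122).

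Two columns match exactly and the third is close: power at 122 is 78.8%. The formula is the one for independent individuals, with a design effect of 1.

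**Allowing for one community per arm.** Let ICC be the share of the variance in *change* that lies between communities. The protocol gives none, so 0.001 to 0.05 is assumed. With m = 122 per arm:
- Design effect DE = 1 + (122 − 1) × ICC.
- Real type I error of the unadjusted 5% test = 2 × [1 − Φ(1.96/√DE)].
- Power, if the ICC were known and allowed for = Φ(difference/(SE × √DE) − 1.96), where SE = √((SD1² + SD2²)/122). SE is 10.398 for physical activity and 1.566 for fasting glucose.

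| Assumed ICC | DE | Type I error | Power, physical activity | Power, fasting glucose | Power, weight |
|---|---|---|---|---|---|
| 0 | 1.00 | 5.0% | 78.8% | 97.3% | 97.9% |
| 0.001 | 1.12 | 6.4% | 74.1% | 95.7% | 96.6% |
| 0.005 | 1.61 | 12.2% | 58.7% | 86.7% | 88.5% |
| 0.01 | 2.21 | 18.7% | 45.9% | 74.5% | 76.8% |
| 0.02 | 3.42 | 28.9% | 32.0% | 55.8% | 58.1% |
| 0.05 | 7.05 | 46.0% | 17.9% | 31.1% | 32.6% |

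Simulating 20,000 null trials at each ICC gave type I errors of 12.6%, 18.7%, 29.7% and 46.9% for ICC 0.005, 0.01, 0.02 and 0.05, in agreement with the formula.

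**Where fasting glucose drops below 80%.** √DE = 6.1 / (1.566 × 2.8016) = 1.390, so DE = 1.93 and ICC = 0.93/121 ≈ 0.0077.

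**Recruiting more people in the same two communities.** As m grows, the variance of the difference tends to 2 × ICC × SD², not to zero. Maximum power for physical activity is then 70.5% at ICC 0.01, and for fasting glucose 70.3% at ICC 0.02.

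**When the ICC is unknown, as here.** Two communities leave 2 − 2 = 0 degrees of freedom, so between-community variance cannot be estimated. The power columns above are therefore optimistic, because they treat the ICC as known.

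**The case against.** The protocol calls itself quasi-experimental, chose communities for their similarity, and compares baseline values between groups. Parts of the programme, such as the walking track and its banners, work at community level, so allocating by community is understandable. The conclusion in the Abstract is hedged. All of this deserves credit. But the label discloses only non-randomisation, and similar demography does not establish zero variance in change.

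Several stronger readings are tempting and are not supported:

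- **That 80% power fails for every outcome.** It does not. Fasting glucose, a primary outcome, keeps it up to an ICC of about 0.0077. The low figures belong mainly to physical activity, which is secondary.
- **That 46% type I error is a forecast.** It follows from an assumed ICC of 0.05. The document supports no particular value.
- **That any standing difference between the communities biases the result.** Outcomes are changes from baseline, so stable differences in level (diet, clinic, food environment) largely cancel. They matter only if they alter the trend.
- **That different field teams measured the two arms.** No section says so. Sections 6.3 and 13.0 describe trained staff and common instruments.
- **That power should be computed on the 85 per arm left after 30% dropout.** Section 12.0 carries the last reading forward, so 122 per arm remain in the analysis. Attrition is a separate matter.
- **That the Gantt entry shows a false claim of randomisation.** It conflicts with 5.6, but it is a clerical point. How the intervention community was chosen is not stated, and choosing it at random would not add degrees of freedom.

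**Conclusion.** The point stands in conditional form. One community per arm is fixed by sections 5.2 and 5.6, and the independence assumption by 5.8 and 12.0. Type I error exceeds 5% at any positive between-community variance in change: about 6% at ICC 0.001, 19% at 0.01 and 46% at 0.05.

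The loss of power depends on the outcome. At ICC 0.005, physical activity falls from 79% to 59% and fasting glucose from 97% to 87%. At 0.01 they reach 46% and 75%. Section 5.8 gives no inputs for 2-hour glucose or HbA1c, so their power cannot be computed, but the type I error figures apply to them at the same ICC.

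The direction is certain once the ICC is above zero. The size rests on an assumed ICC for change, 122 analysed per arm, and a normal approximation. The confounding depends on no ICC value, and no later analysis can remove it.

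**What to change.** Without adding communities:

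1. **Section 5.8.** State that the power is conditional on zero between-community variance in change, and show power by outcome over a stated range of assumed ICCs, as tabulated above.
2. **Section 12.0.** State that p-values and confidence intervals are conditional on these two communities. If an interval widened by √DE is shown, label it an illustration: this design cannot estimate the ICC, and a wider interval does not correct confounding.
3. **Section 13.0 and the Abstract's conclusion.** List the confounding of arm with community. Describe the result as a difference between one intervention and one comparison community, not as proof of effectiveness.
4. **Section 16.0, editorial only.** Remove the word for random allocation from the Gantt entry.

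The cost is protocol wording and one table, with no change to recruitment or procedures. The downside is a more modest conclusion.

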## **5.7 Analysis of outcomes**

The participants will be assessed at baseline, 6th and 12th months after interventions given to them. The plan for data analysis will be described further in subsequent section.

## **5.8 Sample size estimation**

Referring to the study by Kulzer et al [42] using a group based lifestyle intervention study to prevent diabetes mellitus; mean weight loss and duration of physical activity per week were significantly higher while fasting glucose was significantly lower in the intervention group compared to the control group after 12 months follow up. Using the sample size calculation from STATA

program, with power of 80% and significant level preset at 0.05, using different indicators, the calculated sample sizes are as the following:

|                                        | Duration of physical activity (minutes) | Fasting blood glucose (mg/l) | Weight loss (kg) |
|----------------------------------------|-----------------------------------------|------------------------------|------------------|
| Mean difference 1                      | 17.9                                    | 1.8                          | 3.8              |
| Mean difference 2                      | 46.6                                    | -4.3                         | 1.4              |
| Standard deviation 1                   | 63.8                                    | 13.1                         | 5.2              |
| Standard deviation 2                   | 95.5                                    | 11.3                         | 4.1              |
| Calculated Sample size group 1         | 122                                     | 64                           | 60               |
| Calculated Sample size group 2         | 122                                     | 64                           | 60               |
| Final sample size (with 30% attrition) | 122 x 2 = 244                           | 83 x 2 = 166                 | 78 x 2 =156      |

Based on the above, the largest sample size will be used in this proposed study to ensure adequate power for most outcome measures. Therefore, 244 subjects will be require for this study.

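### The 244 target is labelled as allowing for 30% attrition, but the physical activity column that sets it was never inflated; after that loss, power for this secondary outcome is about 63–65%, not 80%

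*Protocol*

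**What the plan says.** Protocol section 5.8 (Sample size estimation) takes means and standard deviations for three outcomes from one published group-based lifestyle study. It computes a size for each "with power of 80% and significant level preset at 0.05".

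- Calculated size per group: 122 for duration of physical activity, 64 for fasting blood glucose, 60 for weight loss.
- Final row for physical activity: "Final sample size (with 30% attrition) | 122 x 2 = 244".
- Final row for the other two outcomes: 83 per group (166 in total) for fasting glucose and 78 per group (156 in total) for weight.

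The section then says that "the largest sample size will be used in this proposed study to ensure adequate power for most outcome measures", and so arrives at 244 subjects.

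Sections 4.0 (Objectives) and 6.4 (Outcome measures) list fasting glucose, 2-hour glucose and HbA1C as primary. Physical activity and weight are secondary.

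**The concern.** The final row is labelled as including attrition, yet its physical activity entry equals the calculated size two rows above. The other two entries have been raised by a factor of 1.3. Because the largest entry becomes the trial size, the one column with no allowance is the one that fixes the target. The protocol therefore implies 80% power after 30% loss for the outcome on which it rests the sample size, and its own numbers do not give that.

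What is at stake is how a physical activity result would be read. A non-significant difference could be presented as coming from an adequately powered comparison. The stated basis for the sample size would also not survive a check by an ethics committee or a journal.

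**Working it through.** **Inputs, all from the table in section 5.8**

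- Physical activity: "Mean difference 1 | 17.9" and "Mean difference 2 | 46.6", so the difference is 28.7 minutes; "Standard deviation 1 | 63.8" and "Standard deviation 2 | 95.5".
- Fasting glucose: 1.8 and −4.3 (difference 6.1); SDs 13.1 and 11.3.
- Weight loss: 3.8 and 1.4 (difference 2.4); SDs 5.2 and 4.1.
- Power 80%, "significant level preset at 0.05". Sidedness is not stated. I take it as two-sided, because a one-sided test gives only about 100 per group for physical activity.

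**Step 1. Reproduce the plan's sizes.** Two SD conventions are plausible.

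- Simple average SD with a noncentral-t calculation. For physical activity the SD is (63.8 + 95.5)/2 = 79.65, and the smallest n reaching 80% is 122. The same method gives 64 and 60 for the other outcomes, so all three columns reproduce.
- Unequal-variance normal formula, n = (1.960 + 0.842)² × (SD1² + SD2²)/difference²:
  - physical activity: 7.849 × 13190.7/823.7 = 125.7, so 126
  - fasting glucose: 7.849 × 299.3/37.21 = 63.1, so 64
  - weight: 7.849 × 43.85/5.76 = 59.8, so 60

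So 122 follows from the table's inputs under a consistent convention, as a size with no attrition in it.

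**Step 2. Could 122 already contain the allowance?** It would then rest on a base of 122/1.3 = 94 or 122 × 0.7 = 85 per group. Power at those sizes on the table's inputs is about 67–70% and 63–65%. Neither is 80%, so no allowance is hidden in the figure.

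**Step 3. Power after the stated loss.** 122 × 0.7 = 85.4, so about 85 per group.

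| Outcome | Per group | Root-mean-square SD (t / normal) | Average SD (t / normal) |
|---|---|---|---|
| Physical activity | 122, no loss | 78.5% / 78.8% | 80.0% / 80.4% |
| Physical activity | 85 | 63.0% / 63.5% | 64.6% / 65.1% |
| Fasting glucose | 85 | 89.8% / 90.2% | 90.0% / 90.3% |
| Weight | 85 | 91.4% / 91.6% | 91.7% / 92.0% |

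Every row treats participants as independent and compares completers only.

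**Step 4. What an allowance would have required.**

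- Dividing by the retained fraction: 122/0.7 = 174.3, so 175 per group, 350 in total.
- By the plan's own factor: 122 × 1.3 = 158.6, so 159 per group, 318 in total.

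**Step 5. The inflation in the other columns.** Multiplying by 1.3 does not offset a 30% loss: 83 × 0.7 = 58 completers against 64 needed, and 78 × 0.7 = 55 against 60. Dividing by 0.7 gives 64/0.7 = 92 and 60/0.7 = 86 per group. Enrolling 122 per group covers both, so the target does not change.

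**The case against.** Several arguments on the other side are sound.

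- **The claim is only about most outcomes.** Section 5.8 does not promise adequate power for every measure, and on the table's inputs the other two sizing outcomes stay near or above 90% after 30% loss. That stands and limits the severity. It does not rescue a row that says attrition is included where it is not.
- **Sizing on the largest requirement is cautious.** It gives fasting glucose more participants than its own column asks for. That stands: using a secondary outcome to set the target is not in itself an error.
- **The analysis is not of completers.** Section 12.0 plans intention-to-treat with last readings carried forward and repeated-measures ANOVA, so 63–65% is conditional. Carrying forward does not restore 80%, however. Suppose, as an assumption, that the 30% lost carry their baseline value forward (zero change). The difference shrinks to 0.7 × 28.7 = 20.09 and each variance becomes 0.7 × SD² + 0.21 × mean². At 122 per group the power is then about 61%.
- **The scale differs.** The table is in minutes, whereas section 6.3 scores activity in MET-minutes per week and categories. The percentage therefore describes the plan's own sizing calculation and does not transfer directly to the measured endpoint.

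A reader might also infer two stronger things that the document does not support. One is that 122 is a miscalculation for 126; step 1 shows that 122, 64 and 60 all follow from one consistent method. The other is that the trial is too small for its primary glucose outcomes. The missing allowance does not show that: of these outcomes the table covers only fasting glucose, and its power stays at about 90% under the plan's own assumptions.

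**Conclusion.** The point holds for the physical activity column. The figure of 244 contains no attrition allowance for the outcome that sets it. After the stated 30% loss, power for that secondary outcome is about 63–65% against the stated 80%, a shortfall of 15 to 17 percentage points. This rests on the table's means and SDs, a two-sided 0.05 test, two equal groups, completers only and independent individuals. The range reflects the two SD conventions and the t or normal calculation.

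The multiplication by 1.3 in the other columns is a slip of method with no effect on the target.

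The figures of about 90% for fasting glucose and 91–92% for weight need a caution. Sections 5.2 and 5.6 allocate by community, with two communities and so one per arm, and these figures ignore that. The document gives no intracluster correlation. If it were 0.01 to 0.05 (my assumption), the design effect 1 + 84 × ICC would be 1.84 to 5.20, and fasting glucose power at 85 per group would fall to about 66% to 29%, even with individual-level degrees of freedom.

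This should be fixed. It is not critical, because the outcome affected is secondary and the remedy changes no design element.

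**What to change.** Restate section 5.8 and keep 244.

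- Delete the statement that 244 includes 30% attrition for physical activity. Say instead that, after 30% loss, about 85 per group remain and power for that outcome is about 63–65%, with the assumptions named.
- Inflate the other two columns by dividing by 0.7: 92 per group (184 in total) for fasting glucose and 86 per group (172 in total) for weight.
- Justify 244 on fasting glucose, a primary outcome, whose 184 it covers.
- If about 90% (fasting glucose) and 91–92% (weight) are quoted, state beside them that they ignore the allocation by community. Otherwise leave them out.
- Leave 122 as it is, and state the formula, the SD convention and the sidedness used: 122 follows from a t calculation with the average SD, 126 from the unequal-variance normal formula.

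The cost is protocol wording only. No participants are added and no procedure changes. One stated power becomes less favourable. The alternative, holding 80% for physical activity after the loss, would mean 318 to 350 participants on the base of 122, and nothing in this point requires it.

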## **2.6 Meta-analysis on 9 randomized controlled trials on efficacy of lifestyle education to prevent type 2 diabetes**

Lifestyle education was effective for reducing both 2-hour plasma glucose and Relative Risk (RR) in high risk individuals and may be useful tool in preventing diabetes. This was proven by a meta-analysis on 9 randomized controlled trials of efficacy of lifestyle education interventions for preventing type 2 diabetes in high risk individuals [27]. The results showed that lifestyle education intervention reduced 2 hour plasma glucose by 0.84 mmol/L (95% CI : 0.39-1.29) compared to the

control group. The one year incidence was reduced by 50% (RR 0.55, 95% CI; 0.44-0.69) compared with the control groups.

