#### **6.4 Outcome measures**

The primary outcome measures for this study are fasting blood glucose, 2-hour plasma glucose and HbA1C. Secondary outcome measures are weight, BMI, waist circumference, Total cholesterol, Triglyceride, LDL cholesterol, HDL cholesterol, Systolic and Diastolic blood pressure, physical activity, diet intake and HRQOL. All these will be taken at baseline, six months and twelve months except for HRQOL that will be measured at baseline and twelve months. The primary assessment time-point of this study is at 6-month to measure the immediate effect of the intervention. The final visit which occurred at 12-month will be used to measure sustainability of the intervention.

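### Section 5.8 claims adequate power for most outcomes, but sizes were calculated for only 3 of 15 outcomes and 1 of 3 primaries, so the claim should be limited to what was calculated

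*Protocol*

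**What the plan says.** Section 5.8 takes effects and standard deviations from one cited group-based lifestyle study and calculates a size "with power of 80% and significant level preset at 0.05" for three indicators: 122 per group for physical activity, 64 for fasting glucose and 60 for weight loss. The last row of the table is labelled as including 30% attrition. It shows 83 and 78 per group for fasting glucose and weight, but leaves physical activity at 122. The section then adopts 244 in total because "the largest sample size will be used in this proposed study to ensure adequate power for most outcome measures".

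Section 6.4 states: "The primary outcome measures for this study are fasting blood glucose, 2-hour plasma glucose and HbA1C". It adds 12 secondary outcomes: weight, BMI, waist circumference, total cholesterol, triglyceride, LDL, HDL, systolic and diastolic blood pressure, physical activity, diet and quality of life.

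Section 2.6 reports that, in a meta-analysis of nine randomised trials, lifestyle education "reduced 2 hour plasma glucose by 0.84 mmol/L (95% CI : 0.39-1.29"). Section 5.8 does not use this figure, and no standard deviation accompanies it.

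**The concern.** The sentence in section 5.8 affirms a property of the trial, and the table beside it supports that property for a minority of outcomes only. Taking the largest of three calculated sizes protects those three. It protects another outcome only if that outcome's standardised difference is large enough, and section 5.8 gives no effect or standard deviation for the other 12, two of which are primary.

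A reader of a non-significant 2-hour glucose or HbA1C result could rely on the stated adequacy and take the result as evidence of no effect. The claim is also thinner than it looks for physical activity, because the column that fixes the total carries no allowance for the loss the protocol itself expects.

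**Working it through.** **1. Count.** Section 6.4: 3 primary + 12 secondary = 15 outcomes. Calculated: 3 of 15 (20%), and 1 of 3 primaries. A majority would be at least 8. Crediting BMI and waist circumference to the weight calculation gives 5 of 15, still a minority.

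**2. Reproducing the table.** Inputs are the section 5.8 means and standard deviations. I take the 0.05 level as two-sided (the protocol does not say), 80% power and 1:1 groups.

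- SD = √[(SD₁² + SD₂²)/2]; d = |mean₁ − mean₂| / SD; n per group = 2 × (1.96 + 0.84)² / d², rounded up.
- Fasting glucose: 6.1 / 12.23 gives d = 0.499 and n = 64 (stated 64).
- Weight: 2.4 / 4.68 gives d = 0.513 and n = 60 (stated 60).
- Physical activity: 28.7 / 81.21 gives d = 0.353 and n = 126 (stated 122). This is close but not reproduced; one-sided testing (100) and 90% power (169) do not reproduce it either.

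**3. Attrition row.** 64 × 1.3 = 83 and 60 × 1.3 = 78, as stated. The same factor on 122 would give 159 per group (318 in total), and dividing by 0.7 would give 175 (350). The table shows 122 × 2 = 244, so no allowance was added.

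**4. Power at the adopted size.** Power = Φ(d × √(n/2) − 1.96), at 122 per group and at 122 × 0.7 ≈ 85:

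| Outcome | 122 per group | 85 per group |
|---|---|---|
| Fasting glucose | 97.3% | 90.2% |
| Weight | 97.9% | 91.6% |
| Physical activity | 78.8% | 63.5% |

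After 30% loss, at least 80% power is shown for 2 of 15 outcomes.

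**5. What an uncalculated outcome would need.** Difference detectable with 80% power = (1.96 + 0.84) × √(2/n) = 0.36 SD at 122 per group and 0.43 SD at 85.

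**6. Illustration for 2-hour glucose, under assumed SDs.** The effect of 0.84 mmol/L is from section 2.6. The SDs are my assumptions; the protocol gives none.

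| Assumed SD (mmol/L) | 122 per group | 85 per group |
|---|---|---|
| 1.5 | 99.2% | 95.5% |
| 2.0 | 90.7% | 78.2% |
| 2.5 | 74.7% | 59.1% |
| 3.0 | 59.0% | 44.6% |

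Power drops below 80% only if the SD exceeds 0.84 / 0.359 ≈ 2.34 (122 per group) or 0.84 / 0.430 ≈ 1.95 (85 per group).

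**7. HbA1C.** The protocol gives neither an effect nor an SD. Under assumed differences of 0.1 to 0.2 percentage points and SDs of 0.3 to 0.6, power runs from 26% to above 99% at 122 per group and from 19% to 99% at 85. The document cannot narrow that range.

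All these figures, like those of section 5.8, treat participants as independent. Section 5.6 allocates by community, with one community per arm.

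**The case against.** The sentence is hedged with 'most', follows directly from the table, and does not say that 2-hour glucose or HbA1C reaches 80%. The adopted size rests on the smallest of the three standardised effects (0.35, against 0.50 and 0.51), so letting a secondary outcome drive it made the trial larger. Fasting glucose, a primary outcome, is well powered even after 30% loss. Power calculations for every secondary outcome are not usually expected, and some outcomes overlap: BMI follows from weight, and LDL is computed from the other lipids. All of this stands. It narrows the gap to two uncalculated primaries and one overstated sentence, but it does not turn 3 of 15, or 1 of 3, into most.

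Section 12.0 plans an intention-to-treat analysis with last values carried forward, so 85 per group is the number with observed follow-up, not the planned number analysed. That is right, but carried-forward values may dilute the effect, so the 122-per-group figures should not be assumed to hold under loss. Section 12.0 also requires 95% confidence intervals, which lessens the risk of misreading a null result; the power sentence still invites it.

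A reader might go further and infer that the trial is underpowered for 2-hour glucose, or that the claim fails on the protocol's own 0.84 mmol/L. The documents do not support that. Without an SD the answer turns on an assumption, and at an SD of 1.5 mmol/L power is at least 95% at either size. Planning on the lower confidence limit of 0.39 mmol/L would give 17% to 53% across SDs of 1.5 to 2.5, but nothing in the protocol makes that limit the design effect.

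**Conclusion.** The concern holds as a point about an unsupported statement. Sizes were calculated for 3 of 15 outcomes and 1 of 3 primaries. Adequate power for 2-hour glucose and HbA1C is not demonstrated; it is not shown to be absent. Physical activity, which sets the 244, has about 79% power with complete data and about 64% after 30% loss, because its column carries no attrition allowance.

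The power figures for the three calculated outcomes rest on the section 5.8 inputs, a two-sided 0.05 level and independent participants. The 0.36 SD and 0.43 SD thresholds rest on the same level and on independence, so they are best cases under allocation by community. The 2-hour glucose and HbA1C power figures are illustrations under assumed values and carry no weight in the conclusion. The trial is not invalidated; a stated power property needs correcting.

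**What to change.** Replace the sentence on adequate power in section 5.8 with a paragraph such as:

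> The size is set by physical activity, for which 122 per group gives about 79% power with complete data and about 64% if 30% are lost. For the same two cases it gives about 97% and 90% power for fasting glucose, and about 98% and 92% for weight. No calculation was made for 2-hour plasma glucose, HbA1C or the other secondary outcomes; for these, the difference detectable with 80% power is at best 0.36 SD (122 per group) or 0.43 SD (85 per group). All these figures treat participants as independent, which allocation by community does not guarantee. Non-significant results on the outcomes without a calculation are interpreted by their confidence intervals, not as absence of effect.

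In the table, note that the physical activity column includes no attrition allowance. If the sponsor has an effect and SD for 2-hour glucose and HbA1C, adding them with their source would be better than the generic threshold.

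The cost is one paragraph and a table note. Enrolment, design and analysis are unchanged; the stated power becomes less favourable.
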